### Sample size {14}

Prior to the beginning of the study, a formal power analysis was done. The plan is to enroll 1000 smokers in 14 clinical sites where specialty tobacco use disorder services (STUDS) are being offered and 200 smokers in 3 clinics in the TAU clinical sites and expect a dropout rate of 50%. Thus, a cluster-randomized study design was envisioned. If we assume that the intervention sites achieve a 25% success rate at achieving abstinence and the TAU group a 5% success rate, then with a reasonably sized intra-cluster correlation coefficient of 0.05, the power to detect a difference in success rate is 99.4%. This assumes a two-sided test of proportions (using a large sample approximation and the corresponding cluster adjustment) with a significance level of 5%.

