## Assignment of interventions: allocation

### Sequence generation {16a}

Block randomization will be by cluster using the program calculator.net. Each clinical site is a cluster, and there will be a 5:1 ratio in the assignment of *both* LACDHS and LACDMH clinics assigned to the intervention arm (offering STUDS) as compared with the TAU arm. A total of 18 study sites will be randomized on a 5:1 intervention to TAU ratio basis, with three TAU sites and fifteen intervention sites split as follows: 11 primary care clinics (9 intervention, 2 TAU) and 7 mental health clinics (6 interventions, 1 TAU).

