## Statistical methods

### Statistical methods for primary and secondary outcomes {20a}

Final analyses will begin in year 4 at quarters 2 and 3. Data analysis will utilize an intention-to-treat (ITT) approach as the primary analysis. An additional set of analyses will use a per-protocol (PP) paradigm that will only use subjects who attend at least 3, out of four visits, including month 12. Descriptive statistics will include number, percent, and mode for categorical data (gender, race/ethnicity, site, LACDHS/LACDMH, number of visits). Continuous variables of clinical characteristics (number of cigarettes smoked, number of years smoked, Fagerstrom score) and Behavioral Measures Battery will be used to describe the study population. Non-normal distribution will be transformed to satisfy the normality assumption for the parametric statistical tests. Scale variables will be presented as min, max, and median. Graphical presentations (histograms, boxplots, and spaghetti plots) will be used to facilitate the visualization of data and the time trend of endpoints and baseline variables. All statistical analyses will be performed using SAS 9.2 and a *P*-value <0.05 will be considered statistically significant.

For model 1, we will perform an analysis of covariance with the baseline value (site, racial-ethnic group, number of visits, age, weight, smoking status, and survey scores) as the covariate and compare the value at the end of the study. To evaluate the change over time between the groups that incorporates all the measures collected over the timeframe of the study, then a two-way repeated measures analysis of variance model will be used. For model 2, a multiple logistic regression model would be built using independent variables such as treatment group and pre-determined baseline covariates (including study site). We posit that using a covariate-adjusted model to evaluate outcome provides a sensitivity analysis for the primary results of a simple comparison of the achievement of smoking cessation. For both models, the analyses will incorporate the cluster-randomized design into the model using an appropriately chosen variance-covariance structure (up to the use of an unspecified structure). In addition, the models will include a term for LACDHS versus LACDMH sites and their interaction with the intervention group.

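### The clause that brings in clustering does not cover the primary simple comparison of cessation, in conflict with the cluster-adjusted test assumed for power; run as worded, a 5% test would reject a true null about 20–35% of the time

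*Protocol article*

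**What the plan says.** All references are to the protocol article.

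- **Statistical methods {20a}** ranks the analyses. The covariate-adjusted model "provides a sensitivity analysis for the primary results of a simple comparison of the achievement of smoking cessation", so the simple comparison is primary and the model supports it.
- The same section then says: "For both models, the analyses will incorporate the cluster-randomized design into the model using an appropriately chosen variance-covariance structure". The two models are model 1 (analysis of covariance and repeated measures) and model 2 (multiple logistic regression). The term for health services versus mental health department is likewise promised for the models.
- A P-value below 0.05 "will be considered statistically significant".
- **Sample size {14}** assumes a "two-sided test of proportions (using a large sample approximation and the corresponding cluster adjustment") at the 5% level. Its inputs are that "intervention sites achieve a 25% success rate at achieving abstinence and the TAU group a 5% success rate", and "with a reasonably sized intra-cluster correlation coefficient of 0.05, the power to detect a difference in success rate is 99.4"%.
- **Sequence generation {16a}** randomises 18 clinics "with three TAU sites and fifteen intervention sites": 9 and 2 in primary care, 6 and 1 in mental health.
- **Section {20c}** keeps every participant in the primary analysis by last value carried forward.

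**The concern.** Whole clinics are randomised, so quit outcomes within a clinic are correlated, and a test that treats participants as independent understates the standard error. Section {20a} attaches the clustering provision to the two models and leaves out the one comparison it calls primary. The sample size section attaches a cluster adjustment to a test of proportions, but only to describe a power calculation. An analyst who follows the analysis section would run an unadjusted test for the headline result, while one who follows the sample size section would not.

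At stake is the main claim of the trial. The Discussion says that the services will continue if found effective, so a false positive on cessation would have practical consequences.

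**Working it through.** **Inputs.** Clinics 15 versus 3 ({16a}); 14 versus 3 in the power text ({14}). Participants 1000 versus 200 ({14}), all analysed under last value carried forward ({20c}); 500 versus 100 if the 50% dropout in {14} is removed. ICC 0.05, rates 25% and 5%, two-sided 5% ({14}). Assumed here: an alternative ICC of 0.01, common null quit rates of 5%, 15% and 25%, and (near-)equal clinic sizes within an arm.

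**1. The stated power.** Design effect DE = 1 + (m − 1) × ICC, followed by a z test with unpooled variance, 14 versus 3 clinics:

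- 500/100: m = 35.7 and 33.3, DE = 2.74 and 2.62, effective n = 182.8 and 38.2, SE = √(0.25×0.75/182.8 + 0.05×0.95/38.2) = 0.0476. Power = Φ(0.20/0.0476 − 1.96) = 98.7%.
- 1000/200: DE = 4.52 and 4.28, SE = 0.0432, power 99.6%.

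Both are close to the stated 99.4%. With variance pooled under the null, the figures are 88.2% and 94.7%, so the stated figure fits a design-effect z test with unpooled variance.

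**2. Type I error if the simple comparison ignores clinic.** With 15 versus 3 clinics, m is the same in both arms, and the true level is 2 × [1 − Φ(1.96/√DE)].

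| Analysed | m | ICC | DE | Formula | Simulated |
|---|---|---|---|---|---|
| 1000/200 | 66.7 | 0.05 | 4.28 | 34% | 33–35% |
| 500/100 | 33.3 | 0.05 | 2.62 | 23% | 20–23% |
| 1000/200 | 66.7 | 0.01 | 1.66 | 13% | 12–13% |
| 500/100 | 33.3 | 0.01 | 1.32 | 9% | 8–9% |

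The simulated column is a beta-binomial null simulation with at least 20,000 runs per setting.

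**3. Type I error if the test in {14} is used,** with the ICC estimated from the data (simulated, ICC 0.05, 15 versus 3 clinics):

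- pooled-proportion variance: about 5–7%;
- unpooled variance: about 8–11%;
- ICC treated as known: 4.0–5.0%, which an analysis of the data cannot assume.

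**4. Tests that hold the level.**

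- A clinic-level t test on 18 − 2 = 16 df rejects a true null 4.4–5.1% of the time in the settings run.
- A permutation test within department has C(11,2) × C(7,1) = 55 × 7 = 385 allocations. Its smallest P is 1/385 = 0.0026, and 19/385 = 4.9%, so a 5% level is attainable.

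**5. Power at 25% versus 5%, ICC 0.05.** Clinic-level t test: 91% (1000/200) and 83% (500/100). Stratified permutation test: 90% and 81%. For comparison, cluster-adjusted z tests with an estimated ICC reach about 93–97% at 1000/200, so they also fall short of 99.4%.

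**The case against.** The best reply is that the protocol describes a cluster-randomised trial throughout, and that the only test of proportions it spells out carries a cluster adjustment. The sentence on the simple comparison stands beside the description of model 2, and the clustering sentence follows directly. The simple comparison could then mean the same clustered analysis without covariates. This has force: a reader might infer a settled plan to ignore clustering, and the documents do not support that. They show two sections that conflict. It does not remove the point, because the analysis section names the primary comparison and the scope of the clustering clause, and the first lies outside the second.

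A reader might also infer that the trial has planned a large-sample reference that fails with three usual-care clinics. That goes too far. The large-sample approximation appears only in the power calculation. The article fixes no reference distribution or variance estimator for the analysis, and such details may properly stand in the SAP. For that test the inflation is modest.

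Two further arguments should not be used. An uncorrected robust-sandwich z test would reject about 18–20% of the time, but no section names that method. The remark that usual-care variance rests on 2 degrees of freedom applies only if that arm's variance is estimated separately, whereas the power text uses one common ICC.

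Finally, 1000/200 is the less favourable sample size. Last value carried forward supports it, but that the ICC stays at 0.05 in that set is an assumption, so both sample sizes are shown.

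**Conclusion.** The point holds as a conflict between the analysis and sample size sections, with a serious consequence on the literal reading of the analysis section. At the protocol's ICC with 15 versus 3 clinics, an unadjusted primary comparison has a false-positive rate of about 33–35% (1000/200) or 20–23% (500/100). At an assumed ICC of 0.01 it is still about 13% or 8–9%. If the sample size section's test is intended, the rate at ICC 0.05 is about 5–7% or 8–11%, depending on the variance form, because only three clinics provide usual care. The figures rest on near-equal clinic sizes, a common null quit rate of 5–25% and beta-binomial variation between clinics. Because this concerns the primary result and can be corrected in a sentence, it should be settled before the final analysis.

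**What to change.** In {20a}, state that the primary comparison of cessation itself accounts for clinic and for the two department strata used in randomisation, and is never tested as if participants were independent. Name a small-sample reference there or in the SAP. Either of these would serve:

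- a clinic-level t test on about 16 df (one fewer if department is fitted as a term);
- a department-stratified permutation test over the 385 allocations.

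Align the sample size section with that test. Reconcile the clinic counts as well, since they set the degrees of freedom and the number of allocations: 15 and 2 in Study setting {9}, 14 and 3 in Sample size {14}, 15 and 3 in Sequence generation {16a}. The 385 applies to the last of these.

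The change costs wording and a little programming. The statistical price is wider intervals and power of about 90% (1000/200) or 83% (500/100) for the t test, slightly less for the permutation test, at 25% versus 5%, in place of the stated 99.4%. Further adjustment for baseline smoking measures is optional and does not bear on the error rate.

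### The cluster adjustment assumed in the power calculation is not carried over to the simple comparison that the analysis section makes primary

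*Protocol article*

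**What the plan says.** The section on statistical methods for primary and secondary outcomes {20a} defines two models. Model 1 is an analysis of covariance, with a repeated-measures analysis of variance for change over time. Model 2 is a multiple logistic regression with treatment group and baseline covariates. The section then ranks the results: the covariate-adjusted model "provides a sensitivity analysis for the primary results of a simple comparison of the achievement of smoking cessation". The next sentence deals with clinics: "For both models, the analyses will incorporate the cluster-randomized design into the model using an appropriately chosen variance-covariance structure". Nothing else in the analysis sections ({20a}, {20b}, {20c} and the interim analyses) mentions clustering.

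The Sample size section {14} describes a "two-sided test of proportions", computed "using a large sample approximation and the corresponding cluster adjustment", "with a reasonably sized intra-cluster correlation coefficient of 0.05". It assumes that the "intervention sites achieve a 25% success rate at achieving abstinence and the TAU group a 5% success rate".

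The Sequence generation section {16a} allocates 15 clinics to the intervention and 3 to TAU, within 11 primary care clinics (9 and 2) and 7 mental health clinics (6 and 1). The missing-data section {20c} makes intention-to-treat with last value carried forward primary, so everyone enrolled is analysed.

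**The concern.** The analysis section gives the headline result to a test that falls outside the scope of its own clustering statement. The power calculation and the analysis section therefore do not describe the same test. An analyst who followed the analysis section literally could compare two proportions across as many as 1200 participants as if they were independent, although only 18 clinics are randomised and only three are TAU. The P value and interval for the main claim would then be too optimistic, and the analyses that do account for clinic would rank below it. The article says that services found effective will continue after the study, so a false positive here has consequences.

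**Working it through.** **Inputs.** 1000 intervention and 200 TAU participants, 50% dropout, 14 v 3 clinics, 25% v 5% abstinence, ICC 0.05, two-sided 5% (Sample size). 15 v 3 clinics (Sequence generation). The clinic counts in the two sections differ, but this barely changes the results.

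**1. Reproducing the stated power of 99.4%.** Design effect DE = 1 + (m − 1) × ICC, where m is participants per clinic. Effective size is n/DE.

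- 1000 in 14 clinics: m = 71.4, DE = 4.52, effective n = 221.2. 200 in 3 clinics: m = 66.7, DE = 4.28, effective n = 46.7.
- Unpooled SE = √(0.25×0.75/221.2 + 0.05×0.95/46.7) = 0.0432. Then 0.20/0.0432 = 4.63, and power = Φ(4.63 − 1.96) = 99.6%.
- With 500/100 completers: DE = 2.74 and 2.62, effective n = 182.8 and 38.2, power = 98.7%.
- With no adjustment at 500/100: SE = √(0.1875/500 + 0.0475/100) = 0.0292, and 0.20/0.0292 = 6.86. Power = Φ(4.90), above 99.9%.

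The stated figure lies between the two cluster-adjusted results and does not match an unadjusted test. A pooled null variance gives less: 94.7% (1000/200) and 88.2% (500/100).

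**2. Type I error if the comparison is not adjusted.** Variance inflation VIF = (DE₁/n₁ + DE₂/n₂)/(1/n₁ + 1/n₂). Type I error = 2 × (1 − Φ(1.96/√VIF)). With 15 v 3 clinics m is the same in both arms, so VIF = DE.

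- 1000/200, ICC 0.05: VIF = 1 + 65.67×0.05 = 4.28, 1.96/2.07 = 0.947, type I error 34.4%.
- 500/100, ICC 0.05: VIF = 1 + 32.33×0.05 = 2.62, 1.96/1.62 = 1.21, type I error 22.6%.

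| ICC | 1200 analysed | 600 completers |
|---|---|---|
| 0.01 (assumed) | 12.8% | 8.8% |
| 0.02 (assumed) | 19.8% | 12.7% |
| 0.05 (protocol) | 34.4% | 22.6% |
| 0.10 (assumed) | 47.6% | 34.1% |

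Beta-binomial simulation (40,000 replicates, null quit rates 5–25%) agrees: 33–35% and 20–23% at ICC 0.05, and 12–13% and 8–9% at ICC 0.01.

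**3. Tests that allow for clinic.** In simulation at ICC 0.05, a t-test on clinic proportions (16 df for 15 v 3) rejects in 4.5–5.0% of null runs. A cluster-robust z-test with no small-sample correction still rejects in about 18–20%, because the TAU variance rests on three clinics.

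**4. Power of the clinic-level t-test.** Simulated power for 25% v 5% at ICC 0.05 is about 91% (1000/200) or 83% (500/100). Part of the fall from 99.4% comes from pooling the variance. The 15 intervention clinics dominate the pooled estimate, and their binomial variance is larger (0.1875 v 0.0475). The same feature separates the pooled from the unpooled results in step 1.

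**The case against.** The best defence is that the word simple contrasts with covariate adjustment, not with cluster adjustment. The only other two-group test of cessation in the article is the test of proportions in the Sample size section, and that test is cluster-adjusted. Its stated power cannot be obtained without the adjustment. The article calls the trial cluster-randomised throughout, so the authors clearly knew that clinics are the unit. The exact form of the test may also sit in a fuller document that is not shown.

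Much of this stands. A reader might infer that the plan fixes a primary test that ignores clinics, with a type I error of 20–35%. The documents do not support that. The analysis section is silent on clinics for the simple comparison, the Sample size section points the other way, and the inflation depends on both an unadjusted test and the true ICC.

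Two things are not answered. First, this is more than an omitted detail: the article itself ranks the simple comparison first and limits its clustering statement to the two models. Second, pointing back to the Sample size section does not settle the test. Its adjustment is a large-sample one, and with three TAU clinics at least one common test of that kind does not hold its level.

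**Conclusion.** The point holds as a mismatch between two sections: the cluster adjustment used for power is not attached to the comparison named as primary. The consequence is conditional. With an unadjusted participant-level test, type I error would be about 33–35% at ICC 0.05 when all 1200 are analysed, which is the set that the missing-data section makes primary. It would be about 20–23% with 600 completers, and about 12–13% and 8–9% at an assumed ICC of 0.01. It exceeds 5% at every ICC tried. The figures assume near-equal clinic sizes, and that the planning ICC applies to the carried-forward outcome, for which the article gives no ICC.

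**What to change.** In section {20a}, state that the primary comparison of cessation and every other between-arm test, including those for primary aim 2, account for clinic. Name a primary test that is valid with three TAU clinics. Two candidates are:

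- a t-test on clinic quit proportions with clinic-level degrees of freedom (15 + 3 − 2 = 16), reporting the risk difference with its clinic-level interval;
- a permutation test over the allocations that the design allows. Choosing 2 TAU clinics of 11 gives 55 ways and 1 of 7 gives 7 ways, so there are 55 × 7 = 385. This option respects the split between primary care and mental health clinics; the plain t-test does not.

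Then restate the power in section {14} for the chosen test and for the number of clinics actually randomised.

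The cost is a few sentences and no new data. Intervals will be wider than from an unadjusted comparison. With the clinic-level t-test, expect power of about 91% (1000/200) or 83% (500/100) in place of 99.4%.

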## Trial design {8}

The study design consists of a 5-year implementation, cluster-randomized comparative effectiveness trial comparing intervention clinics with TAU. Intervention clinics provide smoking cessation group counseling and medication management and are integrated into primary care and community mental health clinics. TAU offers information about the California Smoker’s Helpline and usual provider and clinician counseling. Participants in TAU will be asked at each data collection point (baseline, 3, 6, and 12 months) about any smoking cessation services received including prescribed and over-the-counter smoking cessation medication. Each clinical site in LACDHS is part of a cluster, and there will be a 5:1 ratio in the assignment of clinics assigned to the intervention as compared with the TAU. There are eighteen outpatient clinics participating in the study, eleven from LACDHS and seven from LACDMH (see the “Study setting {9}” section for full details of study sites). The present study aims to enroll 1000 participants from the clinics that will offer smoking cessation services and 200 from clinics not offering smoking cessation services. There are four data collection points, baseline, 3 months, 6 months, and 12 months. Each data collection point will take approximately 30–45 min. These interviews will take place at the participant’s primary care clinic or the site associated with where they usually obtain county-provided services.

In the first quarter of year 1, the research team will revise and prepare study material which will include the participant consent forms, participant and clinical staff questionnaires, recruitment documents, and any other related study material. In the second quarter of year 1, year 2, and the first quarter of year 3, the research team will support the implementation of smoking cessation services by providing training to the clinical staff at the intervention site. The research team will meet with the staff at the intervention sites in quarters 2 and 3 of year 1 and quarter 3 of year 2. The intervention will begin in quarter 2 of year 1 and continue through quarter 4 of year 3. The project may continue recruitment if funding remains available.

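### One covariance structure is named for data nested in both visits and clinics, so the group-by-time test need not hold its 5% level

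*Protocol article*

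**What the plan says.** Under Sequence generation {16a} the clinic is the unit of randomisation: "Each clinical site is a cluster", "with three TAU sites and fifteen intervention sites split as follows" between primary care and mental health. Trial design {8} gives the visits: "There are four data collection points, baseline, 3 months, 6 months, and 12 months".

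Statistical methods {20a} names three analyses: an analysis of covariance of the end-of-study value; for change over time between the groups, "then a two-way repeated measures analysis of variance model will be used"; and a multiple logistic regression. Site is among the covariates of the analysis of covariance, and the logistic model uses "pre-determined baseline covariates (including study site". A single sentence then deals with clustering throughout: "the analyses will incorporate the cluster-randomized design into the model using an appropriately chosen variance-covariance structure (up to the use of an unspecified structure". I read an unspecified structure as an unstructured matrix. The section names no clinic random effect, clinic-by-visit term or clinic-level degrees of freedom.

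**The concern.** An unstructured matrix is a device for a few ordered occasions. Across the four visits within a participant it describes the participant level and has no term for participants sharing a clinic.

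The usual way to honour the sentence would be to add a clinic random intercept. That serves an endpoint comparison, but not a comparison of change: a constant clinic effect cancels when a later visit is compared with baseline, so the test still takes its error from participants. If clinics differ in how they change over 12 months, the error term that matches the randomised unit is clinic-by-visit variation.

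With only three TAU clinics, ordinary differences between clinics in their change could then be read as an effect of the intervention. The repeated measures model is the only analysis the article names for change over time between the arms.

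**Working it through.** **Inputs.** 15 intervention and 3 TAU clinics (Sequence generation; Sample size has 14 and 3, Study setting fifteen and two). Four visits. 1000 + 200 enrolled and 50% dropout (Sample size), so 1200/18 = 67 per clinic enrolled and 600/18 = 33 completing. The plan takes its power "with a reasonably sized intra-cluster correlation coefficient of 0.05". Assumed, because the article does not give them: the split of the ICC into constant and visit-varying parts, a within-participant correlation of about 0.5, equal clinic sizes, a continuous outcome and complete data.

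**The plan's own figure.** With 1000 in 14 and 200 in 3 clinics, the design effects 1 + (m − 1) × 0.05 are 4.52 and 4.28. The standard error of the difference is √(0.25 × 0.75 × 4.52/1000 + 0.05 × 0.95 × 4.28/200) = 0.0432, and 0.20/0.0432 − 1.96 = 2.67, giving power of 99.6%. With 500 and 100 completers it is 98.7%. The stated 99.4% lies between, so the ICC and clinic sizes used here are in line with the plan's.

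**What an unstructured matrix would contain.**
- Across participants in a clinic: m(m + 1)/2 parameters, which is 33 × 34/2 = 561 or 67 × 68/2 = 2,278. Eighteen clinics cannot estimate these, and participants have no order.
- Across visits within participant: 4 × 5/2 = 10 parameters, none for clinic.
- Across visits at clinic level: also 10 parameters, and these do carry clinic and clinic-by-visit variation.

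**Why an intercept does not help.** Write an outcome as clinic + clinic-by-visit + participant + residual. In the change from baseline, the clinic and participant terms cancel and clinic-by-visit and residual remain. A clinic random intercept, or a fixed site effect, drops out in the same way.

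**Check by hand, one change.** Let the ICC of 0.05 be 0.04 constant plus 0.01 clinic-by-visit, with residual variance 0.5 × 0.95 = 0.475. The intra-clinic correlation of a change is 0.01/(0.01 + 0.475) = 0.0206. The design effect is 1 + 32 × 0.0206 = 1.66 (33 per clinic) or 1 + 66 × 0.0206 = 2.36 (67 per clinic). The true level of a nominal 5% test, 2Φ(−1.96/√DE), is 12.8% or 20.2%. Simulation of the month-12 change gave 13.2% and 21.0%.

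**Simulation, all three changes jointly.** Group-by-time test by Hotelling's T² on the three changes from baseline, no true effect, ICC 0.05, 3,000 replicates. With complete data this is the unstructured repeated measures test.

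| Correlation of a clinic's effects at two visits | Participant error, 33 / 67 per clinic | Clinic-mean error, 33 / 67 per clinic |
|---|---|---|
| 1.0 (constant) | 4.0% / 4.8% | 4.1% / 5.1% |
| 0.9 | 12.2% / 19.4% | 5.2% / 4.6% |
| 0.8 | 19.1% / 33.4% | 4.9% / 4.5% |
| 0.5 | 39.4% / 61.9% | 4.9% / 5.2% |

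A repeat gave 12% to 40% and 19% to 61% for the visit-varying rows, and 4% to 6% with clinic-level error. A separately written simulation (4,000 replicates) gave 4.6% / 5.3% for constant clinic effects and 18.7% / 36.2% for the 0.04 + 0.01 split. With no clinic effect at baseline and a clinic share of only 0.01 afterwards, independent between visits, it gave 15.2% / 26.1%.

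**The case against.** The strongest reply is that the sentence does commit to incorporating the cluster design. The chosen structure is to be appropriate, and unstructured is a ceiling, not a requirement. A participant-only matrix would break that commitment, and an unstructured matrix across visits at clinic level would satisfy it; the clinic-mean test that holds its level above is of that kind. This stands. A reader might infer that the plan's test does not hold 5%, or that an unstructured matrix must either be impossible to fit or leave clinics out. The article supports neither.

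It also stands that:
- The size of the inflation depends on how far clinic effects vary over visits, which the article does not give. The simulation does not model last value carried forward, which with 50% dropout reduces change.
- The primary outcome is cessation, and the article describes its primary result as a simple comparison, with covariate adjustment as a sensitivity analysis. It does not assign the repeated measures model to primary aim 1.
- Staggered staff training concerns intervention clinics and does not explain drift in TAU clinics. A better reason to expect visit-varying effects is that all participants must smoke at entry, so clinics can differ in abstinence only after baseline.

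That model details belong in a statistical analysis plan is only a partial answer. The article has already fixed how clustering is to be handled, and the ordinary reading that honours its sentence, a clinic random intercept plus unstructured visits, still leaves the group-by-time test on participant-level error.

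**Conclusion.** The point holds as a defect of specification with a real consequence under a common implementation. One structure is named for two levels of nesting. If it is applied across visits within participant, with or without a clinic random intercept, the group-by-time test is sound only when clinic effects are constant over visits. Otherwise its level is roughly 12% to 40% (33 per clinic) or 19% to 61% (67 per clinic) for between-visit correlations of 0.9 to 0.5. These figures rest on the assumptions listed in the check and describe one permitted reading; they are not the error rate of the plan. They concern the change-over-time test only, and say nothing against an endpoint analysis that accounts for clinics as the sentence promises.

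**What to change.** Reword the clustering sentence so that the visit covariance within participant is stated separately from the clinic-level terms.

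- **Repeated measures model:** keep an unstructured covariance across visits within participant. Add random effects for clinic and clinic-by-visit, or an unstructured matrix over visits at clinic level. Test group-by-time against clinic-level variation, with small-sample degrees of freedom suited to 15 v 3 clinics. Analysing clinic mean changes is equivalent.
- **Analysis of covariance and logistic model:** use one exchangeable within-clinic correlation (a clinic random intercept) with small-sample degrees of freedom. This replaces site as a fixed covariate, which is aliased with arm when whole clinics are randomised.
- Remove the allowance for an unspecified structure as the way the cluster design is handled, unless it is stated to act across visits at clinic level.

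The cost is wording and a few lines of code, with no extra data. The price is wider intervals for the change test, because its error then comes from 18 clinics and not from hundreds of participants.
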